The PROGAIN trial was designed as a randomized, open-label, parallel-group superiority trial to evaluate whether perioperative administration of a high-protein PN formulation improves postoperative nitrogen balance compared with a conventional formulation in patients undergoing curative gastric cancer surgery. Nitrogen balance on postoperative day (POD) 5 was selected as the primary endpoint because it is an objective, quantifiable physiological marker of net protein metabolism that can be measured directly from 24-hour urinary urea nitrogen and dietary protein intake, has been used to evaluate perioperative protein supplementation in upper gastrointestinal cancer surgery [13,14,16], and is sensitive to short-term changes in protein delivery on a clinically relevant timescale. Although nitrogen balance has been used as a primary or principal endpoint in perioperative and nutritional randomized trials [17,18], an improvement is not guaranteed by increased protein delivery: in the catabolic state after major surgery, additional amino acids are frequently oxidized rather than retained, and several randomized trials of enriched amino-acid regimens have found no improvement in nitrogen balance [16,18]; the trial therefore tests whether this formulation produces genuine net nitrogen retention. We hypothesize that perioperative high-protein PN will improve nitrogen balance on POD 5, with secondary benefits on nutritional, glycemic, and functional recovery outcomes. The trial is registered at ClinicalTrials.gov (NCT07488611).

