**Caloric target and dose calculation.** The daily caloric target during the intervention period is set at 20 kcal/kg/day, in keeping with current evidence supporting permissive hypocaloric feeding to avoid perioperative overfeeding. Body weight used for dose calculation is determined by body mass index (BMI): actual body weight is used for participants with BMI < 25 kg/m², and ideal body weight—calculated as height (m)² × 23 (a reference body-mass index of 23 kg/m², consistent with recommendations for Asian populations) [21], applied to both sexes—is used for those with BMI ≥ 25 kg/m². The required daily PN volume is back-calculated from the caloric target using the energy density of the assigned product (0.69 kcal/mL for the control and 0.67 kcal/mL for the investigational product), rounded to the nearest 1 mL, and delivered through a volumetric infusion pump. The calculated daily volume is not expected to exceed the manufacturer-stated maximum of 40 mL/kg/day. For a 75-kg participant, the control formulation delivers approximately 68 g of amino acid per day (0.9 g/kg) and the high-protein formulation approximately 84 g (1.1 g/kg); detailed examples are provided in S2 and S3 Tables. These amino-acid amounts represent PN-only delivery; the total protein supply (oral plus parenteral) that forms the basis of the nitrogen-balance calculation is higher, and the between-arm difference should be interpreted as a difference in PN-delivered rather than total protein.

**Stepwise PN delivery schedule.** PN is administered through a peripheral intravenous line; central venous access is not required. Peripheral access was chosen to avoid the infection and thrombosis risks of central venous catheterisation, consistent with the broader Enhanced Recovery After Surgery (ERAS) principle of minimizing invasive perioperative procedures. PN is initiated on the preoperative day (preoperative day −1; POD −1), withheld on the day of surgery (POD 0) because of perioperative anaesthetic and surgical considerations, and resumed from POD 1 through POD 5, for a total of six administration days. The PN dose on each day is delivered as a fixed proportion of the daily caloric target, decreasing stepwise as anticipated oral intake advances: 80% on POD −1, 100% on POD 1, 60% on POD 2 and POD 3, and 50% on POD 4 and POD 5. The stepwise schedule is summarized in Table 3.

**Table 3 pone.0355677.t003:** Stepwise perioperative parenteral nutrition delivery schedule.

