### Outcomes

**Primary outcome.** The primary outcome is the nitrogen balance on POD 5, expressed in grams per day. Nitrogen balance is calculated using the standard simplified clinical formula: N balance (g/day) = [24-hour oral protein intake (g) ÷ 6.25 + 24-hour parenteral nitrogen delivered (g)] − (24-hour urinary urea nitrogen (g) + 4), where oral protein is converted using the divisor 6.25 (protein contains approximately 16% nitrogen by weight), parenteral nitrogen is derived directly from the product-specific nitrogen content (Table 2; 5.21 mg/mL for the control and 6.17 mg/mL for the investigational product) multiplied by the administered volume rather than from the amino-acid mass, and the constant 4 g accounts for non-urinary nitrogen losses through the integument and the gastrointestinal tract [23,24]. POD 5 was selected as the primary endpoint because previous prospective studies of perioperative protein supplementation in upper gastrointestinal cancer surgery have used assessment windows between POD 3 and POD 7, with POD 5 marking the transition from the catabolic phase that peaks within the first 48–72 hours after surgery to the early anabolic recovery phase [13,14,16]. The 24-hour urinary urea nitrogen collection is performed over POD 5 (00:00–24:00) by self-voided collection, since catheters are removed early under enhanced recovery; participants receive standardized instruction, and collection times and total urine volume are recorded as a completeness check, with incomplete collections flagged and handled per the missing-data plan (all participants remain hospitalized through POD 5). Participants with significant non-urinary gastrointestinal losses (high-output drainage, prolonged nasogastric aspiration, vomiting, or anastomotic leak) are flagged for sensitivity analysis. As limitations, the fixed 4 g constant does not capture gastrointestinal losses and completeness was not verified by creatinine; because both apply similarly across the randomized arms, residual error is expected to be non-differential.

**Secondary outcomes — nitrogen balance on POD 3.** To characterize the early trajectory of nitrogen metabolism, nitrogen balance is additionally assessed on POD 3 as a secondary outcome.

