### Statistical analysis

**Analysis populations.** All efficacy analyses are performed in the intention-to-treat (ITT) population, comprising all randomized participants analyzed in the group to which they were allocated. The per-protocol population is defined as participants who completed the planned PN intervention through POD 5, received at least 90% of the planned cumulative allocated PN volume or amino acid dose, completed the POD 5 nitrogen balance assessment, and had no prespecified major protocol deviations; this population will be used for sensitivity analyses of the primary and key secondary outcomes. The safety population comprises all participants who received at least one administration of allocated PN.

**Primary analysis.** The primary outcome is compared between the investigational and control arms using a two-sample t-test, with the between-group mean difference reported with a 95% confidence interval; the Wilcoxon rank-sum test is used as a sensitivity analysis if distributional assumptions are clearly violated. In a prespecified adjusted analysis, POD 5 nitrogen balance is modelled by analysis of covariance (ANCOVA) with treatment arm as the factor and extent of gastric resection and baseline nutritional status as covariates.

**Mechanistic analyses of the primary endpoint.** To separate the arithmetic and metabolic components of the endpoint, prespecified mechanistic analyses compare between arms (a) total nitrogen intake, (b) urinary urea nitrogen excretion, and (c) net nitrogen retention on POD 5, and evaluate nitrogen-utilization efficiency (net retention relative to delivered nitrogen), and, in an exploratory analysis, adjust the primary endpoint for delivered nitrogen as a covariate. Because delivered nitrogen is a post-randomization variable largely determined by treatment allocation, adjustment for it cannot by itself causally separate nitrogen delivery from nitrogen utilization; these analyses are exploratory and descriptive, use already-recorded variables, and are reported with 95% confidence intervals as hypothesis-generating without causal claims. The partial dependence of nitrogen balance on nitrogen intake is acknowledged as a limitation that these analyses are designed to characterize.

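### Two of the planned mechanistic analyses do not help to separate intake from metabolism: net nitrogen retention repeats the primary contrast, and the efficiency ratio has the wrong null

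*Protocol article*

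**What the plan says.** The primary endpoint (Outcomes, Primary outcome) is nitrogen intake, oral plus parenteral, minus the sum of UUN and a constant: "24-hour urinary urea nitrogen (g) + 4), where oral protein is converted using the divisor 6.25". The Introduction acknowledges that added amino acids are often oxidised after major surgery, and concludes that "the trial therefore tests whether this formulation produces genuine net nitrogen retention".

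The Statistical analysis section (Mechanistic analyses of the primary endpoint) then sets out analyses meant to split the endpoint into its arithmetic and metabolic parts. Between-arm comparisons are planned for (a) total nitrogen intake, (b) UUN and ("c) net nitrogen retention on POD 5". In addition the trial will "evaluate nitrogen-utilization efficiency (net retention relative to delivered nitrogen"), and an exploratory model adjusts the endpoint for delivered nitrogen. The section warns that this adjustment cannot establish a causal split. It labels the whole set exploratory, descriptive and hypothesis-generating, and concedes that balance depends partly on intake. It does not define net retention separately from the balance, and it gives no caution about how the ratio behaves.

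**The concern.** The arms differ in delivered nitrogen by design, so part of any difference in balance is simply intake. The mechanistic analyses are there to show whether the extra nitrogen was kept or excreted. An analysis serves that purpose only if it takes a known null value when none of the extra nitrogen is kept, and if it adds something to the primary comparison.

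Item (c) appears to be the primary endpoint under another name, so a reader could take it as independent support. The ratio divides a quantity that may be negative by a denominator that is larger in one arm by design. It can therefore move with intake alone. The risk is a reported difference in nitrogen utilization, in either direction, in a trial where all the extra nitrogen was excreted.

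**Working it through.** **Inputs from the protocol article**
- Caloric target (Interventions): "The daily caloric target during the intervention period is set at 20 kcal/kg/day".
- Energy density: "0.69 kcal/mL for the control and 0.67 kcal/mL for the investigational product".
- Nitrogen content (Outcomes): "5.21 mg/mL for the control and 6.17 mg/mL for the investigational product".
- PN coverage: "80% on POD −1, 100% on POD 1, 60% on POD 2 and POD 3, and 50% on POD 4 and POD 5", which sums to 4.0 target-days.
- Assumed SD of balance (Sample size): 5 g/day; enrolment 55 per arm.

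**Inputs not in the document (assumed):** POD 5 mean balance −8 to +2 g/day; body weight 60 kg; oral protein 20 g/day (20 ÷ 6.25 = 3.20 g nitrogen).

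**Step 1. Reproduce the plan's intake contrast.**
- Nitrogen at full target: control 20/0.69 × 5.21/1000 = 0.1510 g/kg; high-protein 20/0.67 × 6.17/1000 = 0.1842 g/kg.
- POD 5 at 50% coverage and 60 kg: 4.53 vs 5.53 g, difference 1.00 g. At 70 kg the difference is 1.16 g.
- Cumulative at 60 kg: 0.03316 × 60 × 4.0 = 7.96 g.

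These match the Sample size section's 1.0–1.2 g/day on POD 5 and roughly 8 g overall.

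**Step 2. Item (c).** Write I for intake and NB for balance, so NB = I − UUN − 4.
- If net retention includes the 4 g, it is NB itself.
- If it omits the 4 g, it is NB + 4 for every participant. A constant cancels in a difference of means and leaves variances and ranks unchanged.

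With the same participants and the same handling of missing values, the difference, confidence interval and test are those of the primary endpoint either way.

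**Step 3. Items (a) and (b).** ΔNB = ΔI − ΔUUN. At 60 kg, ΔI = 0.99 g before rounding up.
- None of the extra nitrogen retained: ΔUUN = 0.99, ΔNB = 0.
- All of it retained: ΔUUN = 0, ΔNB = 0.99.

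These two planned comparisons do separate the components.

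**Step 4. The ratio when none of the extra nitrogen is retained.** Both arms then have the same net retention R, and the ratio difference (high-protein minus control) is R × (1/I_high − 1/I_control). The bracket is negative. The difference is zero only at R = 0, favours high-protein when R < 0 and favours control when R > 0. Total intake is 4.53 + 3.20 = 7.73 g vs 5.53 + 3.20 = 8.73 g.

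| Balance in both arms (g/day) | Ratio, 4 g included: control, high-protein | Difference | Difference, 4 g omitted (R = balance + 4) |
|---|---|---|---|
| −5 | −0.647, −0.573 | +0.074 | +0.015 |
| −2 | −0.259, −0.229 | +0.030 | −0.030 |
| 0 | 0, 0 | 0 | not zero, since R = 4 |
| +2 | 0.259, 0.229 | −0.030 | −0.089 |

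If delivered nitrogen means PN nitrogen only, the −5 row with the 4 g included becomes −5/4.53 = −1.104 vs −5/5.53 = −0.905, a difference of +0.199.

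**Step 5. How often a test of the ratio would mislead.** 4,000 trials were simulated with 55 per arm, balance SD 5, the same balance distribution in both arms, total intake as denominator and the 4 g included (assumed weight mean 62 kg, SD 8; oral nitrogen mean 3.2 g, SD 1).

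| Mean balance (g/day) | Mean ratio difference | Rejections at nominal 5% |
|---|---|---|
| −8 | +0.121 | 16.4% |
| −5 | +0.078 | 10.0% |
| −2 | +0.030 | 6.0% |
| 0 | −0.002 | 5.0% |
| +2 | −0.032 | 6.7% |

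In every scenario the mean of ΔI − ΔUUN stayed within 0.02 g of zero.

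**The case against.** The strongest reply is that the plan already contains the right decomposition. Items (a) and (b) will be reported with confidence intervals, and under zero retention ΔUUN rises as far as ΔI while the primary difference sits near zero. A misleading ratio would stand beside results that contradict it. The analyses are labelled exploratory, and the simulated excess of false positives is modest except at clearly negative balances. The full analysis plan, not shown, may also define net retention and the denominator more closely.

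Much of this stands, and it rules out two stronger readings:
- A reader might infer that the mechanistic analyses as a whole cannot separate arithmetic from metabolism. They can, through (a) and (b).
- A reader might infer that the ratio would falsely favour the high-protein arm because these patients are catabolic. The document does not establish that direction. It gives no expected POD 5 balance, describes POD 5 as the point of transition towards anabolic recovery, and leaves open whether retention includes the 4 g. If it does not, any common balance above −4 g/day tilts the ratio towards control.

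Two parts of the reply do not stand. The caution about causal separation concerns adjustment for delivered nitrogen, not the ratio, and an exploratory label limits the strength of a claim without correcting an index whose null is wrong. Nor does the outcome depend on detail left to the analysis plan: with or without the 4 g, and with total or PN nitrogen as denominator, the ratio differs under zero retention unless R happens to be zero.

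**Conclusion.** The point holds for two elements only. That (c) repeats the primary contrast and that the ratio has the wrong null both follow from algebra and need no clinical assumption. The size of the ratio bias does rest on assumptions about balance, oral protein and weight. At 60 kg and 20 g oral protein, with total intake as denominator, it runs from +0.074 to −0.089 over balances of −5 to +2 g/day, depending also on the 4 g, and it is small near R = 0. The consequence is confined to how nitrogen utilization is interpreted. The primary test, alpha, sample size and estimand are unaffected.

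**What to change.** In the protocol and the analysis plan:
- State that (c) equals the primary contrast, or drop it.
- Drop the between-arm comparison of the per-patient efficiency ratio.
- Base any conclusion on utilization on ΔIntake and ΔUUN, already planned, shown side by side with 95% confidence intervals.
- Optionally add marginal retention, 1 − ΔUUN/ΔIntake, with a Fieller or bootstrap interval, as a descriptive summary. It is 0 when all the extra nitrogen is excreted as urea and 1 when none is, whatever the underlying balance.

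The cost is wording; the data are the same, and recruitment is expected to run until February 2027. The optional index will be very imprecise. The 95% half-width for ΔNB is about 1.98 × 5 × √(2/55) = 1.9 g. Divided by an intake contrast of about 1 g, that is roughly ±1.9 on a scale meant to run from 0 to 1. At the planned 3 g/day effect the index would be about 3. It should therefore not carry the conclusion.

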### Safety monitoring

Adverse events, adverse drug reactions, and serious adverse events are identified throughout the intervention and follow-up period through systematic review by the NST — comprising a clinical pharmacist, a dietitian, a ward nurse, and an attending physician — supplemented by direct enquiry, clinical examination, laboratory monitoring, and review of medical records. Events are graded for severity and assessed for causality by the investigator. Serious adverse events are reported within 24 hours to the pharmacovigilance department of the manufacturer of the investigational and control products and to the institutional review board (IRB), in accordance with applicable Korean regulations. Predefined safety triggers for withholding or reducing the assigned PN are described in the Interventions section. No formal data and safety monitoring board is convened given the single-center design, the short intervention period, and the use of two regulatory-approved PN products with established safety profiles; trial safety is overseen by the principal investigator with periodic review by the IRB.

### Patient and public involvement

Patients and members of the public were not involved in the design, conduct, or reporting of this research. Aggregate trial results will be communicated to participants through their treating physician at the participating institution upon completion of the trial. A schematic overview of the trial conduct, integrating recruitment, randomization, intervention administration, in-hospital assessments, and outpatient follow-up, is provided in Fig 2.

**Fig 2 pone.0355677.g002:**
[figure not shown]
PROGAIN trial flow from recruitment through follow-up. Schematic overview of the trial conduct. Eligible patients are screened, randomized 1:1 to amino acid–enriched (high-protein) peripheral PN or conventional peripheral PN in an open-label, parallel-group design, and receive the assigned PN from preoperative day −1 through postoperative day (POD) 5 alongside standardized perioperative diet advancement. Daily intervention-period assessments include meal intake logs, with blood glucose monitoring on POD 5 and skeletal muscle index assessed from baseline and follow-up computed tomography, and laboratory and functional recovery measures. Outpatient follow-up visits at POD 14 and at 1, 3, 6, and 12 months capture body weight, nutritional indices, mGPS, CAR/PNI, and clinical events. The primary outcome is nitrogen balance on POD 5; secondary outcomes include nutritional, glycemic, complication, and functional recovery measures. CAR, C-reactive protein–to-albumin ratio; mGPS, modified Glasgow Prognostic Score; PN, parenteral nutrition; PNI, Prognostic Nutritional Index; POD, postoperative day.

### Ethics and dissemination

The trial is conducted in accordance with the Declaration of Helsinki, the International Council for Harmonisation Good Clinical Practice guidelines, and applicable Korean regulations. The protocol, the participant information sheet, and the informed consent form have been approved by the IRB of Soonchunhyang University Cheonan Hospital (approval number: 2025-11-024-001); The full IRB-approved study protocol (most recent amended version) is provided as S1 Protocol. IRB approval is obtained for any subsequent protocol amendment before its implementation, and substantial amendments are notified to the trial registry. Written informed consent is obtained from each participant prior to any trial-specific procedure, as described in the Recruitment section.

Trial findings will be disseminated through publication in a peer-reviewed scientific journal in accordance with the CONSORT 2025 statement (an anticipated participant flow diagram prepared from the CONSORT 2025 template is provided as S1 Fig and will be populated at trial completion), through presentations at scientific meetings, and through results reporting on ClinicalTrials.gov upon trial completion. De-identified individual participant data underlying the published results will be made available, on reasonable request to the corresponding author and following review by the institutional data access committee and applicable ethical and regulatory requirements*.*

